### Statistical analysis

SPSS version 16.0 is used for all statistical calculations. A P value of 0.05 is defined as significant. Baseline characteristics are summarized with descriptive statistics. For categorical data the numbers or proportions are given, for normal distributed data the mean and standard deviation and for not normal distributed data the median with percentiles.

Differences between the alfentanil group and the placebo group will be tested for significance. For the calculation of differences in pain scores per position, average, and the maximum pain score during the procedure will be calculated using an independent samples t-test.

Differences in burden of different aspects of the procedure as well as the total procedural burden will be calculated using a chi-square test. Differences in the most burdensome aspect will also be calculated using the chi-square test. Differences in procedural time and recovery time will be calculated using an independent samples t-test.

We will test the associations between the baseline characteristics (independent variables mentioned below) and pain scores. As we consider the pain scores as continuous data, for this approach we will perform linear regression analyses.

Univariate analyses will be performed with pain scores as dependent variable and the following variables as independent variables: age, sex, BMI, education, ethnicity, expected burden, scan indication (including abdominal pain), known diseases and diagnosis, and whether it is the first CT colonography. Subsequently, the variables with a P value < 0.1 will be included in the multivariate analysis. In case more than four variables turn out to result in a P < 0.1, the four most influential variables will be used in the multivariate analysis. A stepwise backward selection strategy will be used, with a P value < 0.05 considered statistically significant.

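### Predictors of pain: nine unadjusted tests give a high chance of a false finding, and stepwise selection separately exaggerates the weak predictors that survive

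*Protocol article*

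**What the plan says.** The Statistical analysis section of the protocol article sets out a regression of pain on baseline characteristics, separate from the comparison of alfentanil with placebo.

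- **Model:** "As we consider the pain scores as continuous data, for this approach we will perform linear regression analyses".
- **Candidates, nine items:** "age, sex, BMI, education, ethnicity, expected burden, scan indication (including abdominal pain), known diseases and diagnosis, and whether it is the first CT colonography".
- **Screen:** each item is first tested alone, and "the variables with a P value < 0.1 will be included in the multivariate analysis".
- **Cap:** "In case more than four variables turn out to result in a P < 0.1, the four most influential variables will be used".
- **Final step:** "A stepwise backward selection strategy will be used, with a P value < 0.05 considered statistically significant".

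The outcome is given only as pain scores in the plural. Earlier, the same section lists, for the randomised comparison, "differences in pain scores per position, average, and the maximum pain score during the procedure", but it does not say which of these the regressions use. The section mentions no multiplicity adjustment for this search and does not call it exploratory. The search is not among the primary or secondary objectives.

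**The concern.** The rule is complete enough to be followed as written. It produces a list of variables described as statistically significant, in the same terms as the randomised comparisons. Two things go wrong, and they need to be kept apart.

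1. **Multiplicity.** Nine items are each given a chance to reach P < 0.05 without adjustment. The chance that at least one does so by luck is far above the chance for any single item.
2. **Selection bias.** The final coefficients come from the same roughly 90 patients who were used to choose the variables. A weak predictor stays in only in samples where its estimate happens to be large, so its reported effect is too big and its interval misses the truth too often.

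At stake is what the trial reports about who has pain during CT colonography. Whether alfentanil works is not at stake.

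**Working it through.** **Inputs from the protocol article.** Nine candidates, screen at P < 0.1, cap of four, retention at P < 0.05 (Statistical analysis); 45 patients per group, so 90 in total, and SD 2.6 (Sample size). The article gives no false-positive rate for this search, so there is no figure of its own to reproduce.

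**Assumptions.** Candidates are normal with a common pairwise correlation, unless stated otherwise. The most influential variables are taken to be those with the smallest P values, since the article does not define the term. True effect sizes are assumed, because the article gives none.

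**Step 1: closed form without any selection.** For nine independent tests at 0.05, the chance of at least one false positive is 1 - 0.95^9 = 1 - 0.630 = 37.0%.

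**Step 2: the stated procedure, simulated with no true predictor** (n = 90, 15,000 runs per row, one pain score). The last column is the mean number of false predictors divided by 9.

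| Correlation between items | At least one false predictor | Mean number of false predictors | Rate per item |
|---|---|---|---|
| 0 | 37.5% | 0.465 | 5.2% |
| 0.1 | 36.7% | 0.444 | 4.9% |
| 0.2 | 35.6% | 0.414 | 4.6% |
| 0.3 | 33.9% | 0.372 | 4.1% |
| 0.5 | 27.0% | 0.275 | 3.1% |

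The result hardly moves with n = 76 (38.0%, independent items), mixed continuous and binary items (37.5%), multi-level factors tested by F-test (37.7%), or a true treatment effect of 1.5 left out of the model (37.5%). More than four items pass the screen in about 0.1% of null runs with independent items and about 3% at correlation 0.5, so the cap almost never acts.

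The independent-item figure of 37.5% matches the 37.0% of Step 1, where there was no selection at all. The count of tests therefore explains it.

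**Step 3: does a full model lower that figure?** The chance of any P < 0.05 under the null is:

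| Setting, nine items | Stated procedure | All items in one model |
|---|---|---|
| n = 86, independent | 38.0% | 35.9% |
| n = 86, correlation 0.3 | 33.9% | 34.4% |
| n = 90, correlation 0.5 | 27.4% | 34.6% |

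It does not. At correlation 0.5 the full model does somewhat worse.

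**Step 4: selection bias, by hand.** For one standardised predictor, SE = 2.6/√90 = 0.274. To be retained alone, its estimate must exceed about 1.987 × 0.274 = 0.545 in size. Suppose the true effect is 0.3.

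- Chance of retention: P(Z > (0.545 - 0.3)/0.274 = 0.894) = 0.186, plus about 0.001 in the wrong direction, so 0.187.
- Mean of estimates beyond the threshold: 0.3 + 0.274 × 0.2675/0.1857 = 0.69, where 0.2675 is the normal density at 0.894.
- The interval misses 0.3 if the estimate exceeds 0.3 + 0.545 = 0.845 (probability 0.0235) or has the wrong sign (0.001). Coverage given retention is 1 - 0.0245/0.187 = 87%.

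**Step 5: selection bias, simulated** (stated procedure, n = 90, one true predictor and eight null items, independent).

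| True effect per SD | Mean retained estimate (absolute) | Ratio to truth | Coverage of 95% CI |
|---|---|---|---|
| 0.3 | about 0.68 | 2.3 | about 87% |
| 0.5 | 0.73-0.75 | about 1.5 | about 95% |
| 0.8 | 0.87 | 1.1 | about 97% |

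In the full model with a true effect of 0.3, the mean estimate is 0.29-0.30 and coverage is 95%.

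**The case against.** The strongest reply is that the selection steps are being blamed for something they do not do. This is correct for the multiplicity figure. Nine plain tests give 37%, and a full model gives much the same. A reader might infer that screening, cap and backward elimination produce the one-in-three chance of a false predictor; Steps 1 to 3 show that they do not.

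A reader might also infer that the plan's error rate is about seven times its stated 5%. The article states a per-test threshold and claims no familywise rate for this analysis. On the per-test scale the rate is 3-5% per item.

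Two larger figures are tempting. If the search were run on all six pain scores, about 78% of null data sets would give a false predictor (assumed correlation 0.6 between positions). If the nine items were split into 14 separate columns, the rate per score would be about 52%. The article fixes neither the outcomes nor the coding of this regression, and an article may leave such details to the full protocol. Neither figure can be charged to the plan.

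Finally, the analysis lies outside every objective, the expected conclusions in the Discussion do not mention predictors of pain, and the rules are openly prespecified. All of this stands and limits the importance of the point. It does not answer the selection bias, or the use of the word significant for unadjusted survivors.

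**Conclusion.** The concern holds as two distinct, modest points.

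- **Multiplicity.** There is about a 34-38% chance of at least one false predictor per pain score if the nine items are independent or correlated up to 0.3, and 27% at correlation 0.5. The cause is nine unadjusted tests. The true correlation between items is not given in the article.
- **Selection bias.** Retained weak predictors are overstated, by a factor of about 2.3 with about 87% coverage at an assumed true effect of 0.3 points per SD. The distortion shrinks as the effect grows and is small at 0.8.

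A reader might think that this weakens the trial's main result. It does not: the primary outcome is compared by an unadjusted t-test, and neither that test nor the sample size uses the regression. This is a minor secondary-analysis point that is cheap to put right.

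**What to change.** In the Statistical analysis section:

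1. Name maximum pain as the single outcome of the predictor regression.
2. Replace the screen, cap and backward selection with one prespecified linear model containing all listed variables, with sparse categories collapsed before unblinding.
3. Report every coefficient with its 95% CI, including those near zero.
4. Label the analysis exploratory and remove the significance wording for it. If significance claims are to be kept, add a multiplicity adjustment over the listed variables.

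Items 2 and 3 deal with the selection bias. They leave the multiplicity where it was, so item 4 is needed as well.

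The change costs only wording and a little computation; no new data are needed. The price is wider intervals. With nine equally correlated items, the variance of a coefficient relative to a one-variable model rises by (1 + 7r)/((1 - r)(1 + 8r)). At r = 0.3 this is 3.1/2.38 = 1.30, so intervals are about 14% wider. At r = 0.5 it is 4.5/2.5 = 1.8, or about 34% wider. Categories that need several columns would widen them further.

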### Ethical approval

Ethical approval was obtained from the Medical Ethics Committee of the Academic Medical Center, Amsterdam, the Netherland (NL35916.018.11). A marginal review was performed by the National Authority, the Central Committee on Research Involving Human Subjects (CCMO), and there were no objections to perform this study (NL35916.018.11 BI).

## Discussion

CT colonography is a structural examination of the colon and rectum. It is used in high risk patients as an alternative for colonoscopy or in case colonoscopy is incomplete or contraindicated. Although CT colonography is less invasive, results on pain and burden during these examinations in literature are variable. Several studies show higher procedural pain and burden for CT colonography compared with colonoscopy with conscious sedation due to air or carbon dioxide insufflation [6-8]. With an appropriate analgesic agent, CT colonography may not only be less invasive, but also less painful and less burdensome, which would be advantageous for patients.

Additionally, the screening test for colorectal cancer is still under debate. Several screening tools are available such as faecal occult blood test, sigmoidoscopy, colonoscopy, and CT colonography. The effectiveness of a screening tool is influenced by both participation and yield. Colonoscopy and CT colonography are the most sensitive techniques for the detection of colorectal neoplasia, i.e. colorectal cancer and its precursor, colorectal advanced adenomas [32]. The advantages of colonoscopy are the highest sensitivity and opportunity for direct polyp removal. Advantages of CT colonography are that this technique is less invasive and has a very low complication rate [33]. CT colonography adherence and participation most likely will be influenced by a clinically relevant reduction in pain and burden experienced during the examination and therefore may have impact on the principal outcome measure of colorectal cancer screening, i.e. the number of advanced neoplasia per 100 invitees.

This RCT will provide evidence whether a single bolus intravenous alfentanil gives a clinically relevant reduction in maximum pain during CT colonography. Furthermore, this study will provide information about the effect of alfentanil on pain and burden of different CT colonography aspects, side effects, adverse events, procedural time and recovery time. We expect a clinically relevant reduction of procedural pain and burden without adverse events and recovery time. This could make CT colonography a more patient-friendly examination and is likely to increase participation for its use as a screening tool.

## Abbreviations

CT: computed tomography; NRS: numeric rating scale; BMI: body mass index; NaCl: sodium chloride; kV: kilo volts; mAs: milliampere second; ICH: The International Conference on Harmonisation of Technical Requirements for Registration of Pharmaceuticals for Human Use; RCT: randomized controlled trial; AMC: Academic Medical Center.
